## Methods/design

### Study design

This is a multicenter, randomized, double-blind, placebo-controlled clinical trial with significant advantages in its overall design. After a 7-day screening period, 140 eligible participants will be randomly assigned in a 1:1 ratio to either the trial group (de-walled GLSP + Osimertinib) or the control group (placebo + Osimertinib) through the Interactive Web Response System (IWRS). All participants will undergo two cycles of targeted and experimental drug therapy, followed by a one-month follow-up period. Visits are scheduled on the last day of every 14 days after enrollment. The study is scheduled to be open from February 2023 until February 2026. Recruitment will commence in August 2023 and last for a duration of 18 months (Fig. 1).

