### Randomization and allocation concealment

The IWRS of the ProResearchCom Intelligent Monitoring System for Clinical Research will be utilized. Upon enrollment of eligible participants, it is obligatory for the Clinical Research Coordinator (CRC) to input participant details into the IWRS. Once verified by either the Principal Investigators (PI) or Sub-Investigator (Sub-I), participants will be allocated to either the trial or control group in a 1:1 ratio. The IWRS will automatically generate unique identification numbers and drug codes for each participant, subsequently providing feedback on grouping results to the PI or sub-I, who will then notify the drug administrator regarding preparation of drugs corresponding to their respective assigned drug codes.

The current study utilizes a double-blind methodology, whereby the de-walled GLSP drinkable tablets and placebo are enclosed in visually indistinguishable cartons utilizing identical pouches. Each carton is allocated a drug number that conceals details regarding the participant’s group and type. Participants will remain unaware of their treatment allocation until the completion of the trial, while statistical analysts have access to complete group information but do not actively partake in the trial.

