#### Secondary outcomes

The secondary outcomes are as follows:

The efficacy evaluation of the combination of de-walled GLSP and EGFR-TKIs will be evaluated based on objective response rate (ORR), disease control rate (DCR), and progression-free survival (PFS) according to RECIST 1.1 criteria. Imaging examinations and efficacy assessments will be conducted on day 0, day 42, and day 84 of the treatment period, calculating ORR/DCR, while PFS will be determined by follow-up at each treatment cycle during the follow-up period.

The QoL assessment will be conducted using the QLQ-C30, PFS-CV (Chinese version of the Piper Fatigue Scale), and EQ-5D (European Five Dimensional Health Scale). Participants will independently complete these three questionnaires with assistance from the investigator to evaluate patients’ QoL from a multidimensional perspective. The total score for QLQ-C30 is calculated by summing scores across domains and dividing by the number of items included, which is further linearly transformed using polarization. PFS-CV measures typical fatigue symptoms and is calculated as the mean sum of all topic scores, with subscale scores obtained by averaging four different dimensions separately. EQ-5D quantifies patient health status through five dimensions assessed via a utility index, while a visual scale allows direct scoring by patients on a scale of 0 to 100. QoL will be collected at baseline and each visit.

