### Data management

The responsibility for data management lies with Beijing Excellence Future International Pharmaceutical Technology Development Co., Ltd. The Data Manager (DM) of the company has implemented Electronic Data Capture (EDC) based on the Case Report Form (CRF) in ProResearch’s Clinical Research Intelligent Monitoring System, following the previously drafted Data Management and Validation Plan. Clinical Research Coordinators (CRCs) can input data into EDC using their accounts. Any errors or queries identified by the system will be forwarded to CRCs for resolution. Once all data entry issues have been resolved, PI, Sub-Is, and CRCs will lock the database within four weeks. Finally, Beijing Excellence Future International Pharmaceutical Technology Development Co., Ltd exports and transfers the locked database to statisticians for analysis purposes. Only the DM has access to the final trial dataset.

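### As written, the randomisation section has the IWRS report the group to the investigator, which conflicts with the double-blind label and the concealing drug numbers

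*Protocol article*

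**What the plan says.** The Study design section of the protocol article states: "This is a multicenter, randomized, double-blind, placebo-controlled clinical trial". The title, the Introduction and the section on randomization and allocation concealment use the same label.

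That last section describes the process in order. The CRC enters the participant's details, the PI or Sub-I verifies them, and the participant is allocated 1:1 to the trial or control group. Once the IWRS has produced an identification number and a drug code, it is described as "subsequently providing feedback on grouping results to the PI or sub-I". The investigator's next step is to pass the drug code on, so that the drug administrator can prepare the matching product.

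The next paragraph describes the masking: "Each carton is allocated a drug number that conceals details regarding the participant’s group and type". On the patients' side, the article promises this: "Participants will remain unaware of their treatment allocation until the completion of the trial". It also says that the statistical analysts hold full group information but take no active part in the trial.

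Three other places bear on the consequence:
- **Primary outcome** sets the endpoint as the QLQ-C30 fatigue subscale score on day 56.
- **Secondary outcomes** says of the QLQ-C30, PFS-CV and EQ-5D: "Participants will independently complete these three questionnaires with assistance from the investigator".
- The **withdrawal criteria** include safety concerns identified by the investigators, and **Statistical analysis** leaves out the data of any participant who meets the withdrawal criteria.

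**The concern.** To dispense a masked product, a site needs the participant's number and the drug code, and nothing else. A system that also sends the grouping result to the PI or Sub-I undoes what the coded cartons are there to do. Thirteen hospitals are to follow this text, so the question is what each of them would do if it followed the text literally.

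Two routes to bias would open:
- **Through the answers.** Fatigue is subjective, and an investigator assists when the scale is completed. A helper who knows the arm can colour how an item is explained or prompted.
- **Through who is analysed.** An investigator who knows the arm may judge a safety withdrawal differently by arm, and withdrawn patients' data then drop out of the comparison.

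Neither kind of bias can be removed at the analysis stage once the data have been collected.

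**Working it through.** The contradiction is one of text, so the main check sets the statements side by side. The arithmetic comes second and is illustrative.

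**1. What group means in this section.** The sentence before the disputed clause allocates participants to the trial or control group. The paragraph after it says that the drug number conceals group and type. In both places group is the treatment arm. Nothing in the section gives the word another sense for the clause in between.

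**2. Who is said to know what.**

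| Role | Statement in the article |
|---|---|
| Participants | Unaware of allocation until the trial is complete |
| Statistical analysts | Hold full group information |
| PI or Sub-I | Receive feedback on grouping results |
| Drug administrator | Notified of drugs by drug code |

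Only the third row conflicts with the double-blind label. The fourth row shows that dispensing runs on the code alone, so the group adds nothing that the procedure needs.

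**3. The plan's own figure.** The Sample size calculation section gives a difference of 15 points, SD 24.9, two-sided alpha 0.05, power 0.90 and 1:1 allocation. With n = 59 per arm:
- standard error = 24.9 × √(2/59) = 4.584
- noncentrality = 15 / 4.584 = 3.272 on 116 degrees of freedom
- power = 0.901

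The exact t-test solution is 58.89 per arm, which rounds up to the stated 59. With 15% dropout, 59 / 0.85 = 69.4, which rounds up to the stated 70. The sample size reproduces, and the blinding point does not depend on it.

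**4. Illustration of sensitivity.** Suppose GLSP has no effect and knowledge of the arm shifts the between-arm mean fatigue score by δ. The probability of a significant result is P(|T| > 1.981), where T is noncentral t with 116 degrees of freedom and noncentrality δ / 4.584.

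| δ (assumed) | Noncentrality | Rejection probability |
|---|---|---|
| 0 | 0 | 0.050 |
| 3 | 0.654 | 0.099 |
| 5 | 1.091 | 0.191 |
| 8 | 1.745 | 0.409 |

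Nothing in the documents informs δ. The table shows what a bias of each size would do to this design. It does not estimate what this clause does.

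**The case against.** **The clause may be loose wording.** Its sentence begins with identification numbers and drug codes and ends with dispensing by drug code. If the group were disclosed, routing a concealing code through the PI would serve little purpose. Grouping results could therefore mean the randomisation output, that is, the number and the code. The article is imprecise elsewhere too: it calls the product granules in one section and drinkable tablets in another. This objection stands to the extent that the text cannot show that investigators are unblinded in practice. It does not rescue the clause, which either describes unblinding or misdescribes a blinded procedure.

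**The patient rates the fatigue.** Participants complete the scales independently, with assistance, and are themselves blinded. Bias would have to pass through a helper to a blinded self-rater, which is weaker than scoring by an unblinded assessor. This stands, and it limits the likely size.

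**The roles are not tied together.** No section says that the PI or Sub-I who receives the result is also the person who helps with the questionnaires or judges withdrawals. Overlap is plausible but is an inference.

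**A condensed article need not list every blinded role.** Agreed. The absence of a sentence naming investigators as blinded is not a fault in itself. The point rests on the positive statement that they receive the grouping result.

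A reader might also infer that tumour response is read by unblinded site staff. The documents do not support that: Secondary outcomes gives RECIST 1.1 and the imaging days but names no reader.

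**Conclusion.** The point holds as an internal contradiction that needs correcting. Followed as written, the clause would disclose the arm to the PI or Sub-I, against the double-blind label and against drug numbers meant to conceal it. Because this is a stated rule and not a missing detail, a fuller protocol would not make the article's wording consistent.

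A reader might go further and conclude that investigators are unblinded. The documents do not establish this, since the code-assignment reading remains open and only the live IWRS display can settle it. Nor do they support an argument that the next allocation could be guessed: no block scheme is stated, and no site investigator is said to see the whole sequence.

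The size of any bias is unknown. The 10%, 19% and 41% error rates depend wholly on assumed shifts of 3, 5 and 8 points and serve only to show that this design is sensitive to modest reporting bias. The importance of the point comes from where the risk falls: a subjective primary endpoint collected with investigator help, and withdrawal judgements that decide whose data are analysed.

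**What to change.** 1. **Replace the clause.** State that the IWRS returns only the identification number and the drug code to the PI, Sub-I, CRC and drug administrator, and does not return the group.
2. **State the blinding.** Add a sentence that investigators, and anyone who helps with questionnaires or assesses outcomes, stay blinded until database lock.
3. **Check the live system.** Confirm what the IWRS displays to each role at each site. If it shows only codes, correcting the wording is enough.
4. **If groups were shown at any site,** stop this, document which patients were affected, and report it as a limitation. Compare affected with unaffected patients only if enough are unaffected. If the clause was applied to every participant, few or none would remain, so a planned analysis that leaves the affected patients out cannot be relied on.

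The text changes amount to two sentences and need no extra patients or visits. The system check should be short. If the display has to be changed, the cost depends on the IWRS configuration, which the documents do not describe.

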### Sample size calculation

The modeling calculations were conducted using the PASS 15.0 software, employing a Two-Sample t-test Assuming Equal Variance (bilateral test) with the following parameters: alpha = 0.05, power = 0.90, and N1:N2 = 1:1 ratio. The score of fatigue according to QLQ-C30 is the primary outcome measure of our study. In the FLAURA patient-reported outcome using the same scale, a mean fatigue score of 32.2 ± 24.9 was observed in patients with advanced EGFR-mutated NSCLC treated with Osimertinib [14]. Referring to previous literature, it is considered that the minimum clinically important difference (MID) in fatigue subscale is 11.1 and there exists a range of change between 11.1 and 22.2 points within this threshold value range for clinical significance assessment purposes [15]. The use of de-walled GLSP is assumed to result in at least a 15-point increase in fatigue score, indicating potential clinical significance for this drug intervention approach. By calculating N1 = N2 = 59 cases, we determined that the minimum required sample size would be 118 cases. Considering a dropout rate of 15%, adjusting N1 = N2 = 70 cases yields a minimum sample size requirement of 140 cases.

### Assessments and time-points

Assessments will be conducted biweekly from the beginning of the study until completion (Table 1).

**Table 1 Tab1:** Trial visit schedule

Study stage		Baseline	Therapeutic period				Follow-up period	
Point of visit			1	2	3	4	5	6
Follow-up time points^a^		7 days before treatment	Day 14 of treatment	Day 28 of treatment	Day 42 of treatment	Day 56 of treatment	Day 14 after treatment	Day 28 after treatment
Time point (days)		-7 to 0	14	28	42	56	70	84
Visit windows (days)		± 3	± 3	± 3	± 3	± 3	± 7	± 7
Informed Consent		×						
Inclusion and exclusion criteria		×						
Demographic data		×						
History of diagnosis and treatment		×						
Blood and stool samples collected		×				×		
Laboratory and aided examination	Liver/ Renal/ Blood/ Urine/ Stoolfunction test	×				×		
	Twelve items of cytokines	×				×		
	Imageological examination	×			×			×
	ECG	×				×		
QLQ-C30/ PFS-CV/ EQ-5D		×	×	×	×	×		×
Evaluation of adverse reactions		×	×	×	×	×		×
AE&SAE		×	×	×	×	×		×
Compliance evaluation		×	×	×	×	×		×
Combination drug		×	×	×	×	×		×

*Abbreviations* ECG electrocardiograph, QLQ-C30 Quality of Life Questionnaire for Cancer Patients, PFS-CV Chinese version of the Piper Fatigue Scale, EQ-5D European Five Dimensional Health Scale, AE adverse events, SAE serious adverse event

^a^Patients will be followed up every two weeks

#### Primary outcome

Fatigue symptoms as adverse reactions to EGFR-TKIs is the primary outcome of this study, which will be evaluated by the EORTC QLQ-C30 Chinese version. The scale will be administered biweekly throughout the treatment period. The outcome endpoint will be determined based on the QLQ-C30 fatigue subscale score on day 56.

#### Secondary outcomes

The secondary outcomes are as follows:

The efficacy evaluation of the combination of de-walled GLSP and EGFR-TKIs will be evaluated based on objective response rate (ORR), disease control rate (DCR), and progression-free survival (PFS) according to RECIST 1.1 criteria. Imaging examinations and efficacy assessments will be conducted on day 0, day 42, and day 84 of the treatment period, calculating ORR/DCR, while PFS will be determined by follow-up at each treatment cycle during the follow-up period.

The QoL assessment will be conducted using the QLQ-C30, PFS-CV (Chinese version of the Piper Fatigue Scale), and EQ-5D (European Five Dimensional Health Scale). Participants will independently complete these three questionnaires with assistance from the investigator to evaluate patients’ QoL from a multidimensional perspective. The total score for QLQ-C30 is calculated by summing scores across domains and dividing by the number of items included, which is further linearly transformed using polarization. PFS-CV measures typical fatigue symptoms and is calculated as the mean sum of all topic scores, with subscale scores obtained by averaging four different dimensions separately. EQ-5D quantifies patient health status through five dimensions assessed via a utility index, while a visual scale allows direct scoring by patients on a scale of 0 to 100. QoL will be collected at baseline and each visit.

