**Method/design:**

A total of 140 participants will be randomly assigned to receive either de-walled GSLP or placebo for a duration of 56 days. The primary outcome measure is the fatigue score associated with EGFR-TKI adverse reactions at week 8, evaluated by the Chinese version of the European Organization for Research and Treatment of Cancer (EORTC) Quality of Life Questionnaire for Cancer Patients (QLQ-C30). Secondary outcomes include evaluation of treatment effectiveness, assessment of quality of life (QoL), and exploration of immune indicators and gut microbiota relationships. Following enrollment, visits are scheduled biweekly until week 12.

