## Introduction

According to GLOBOCAN 2020, mortality of advanced lung cancer already accounts for 18.0% of that from overall cancer, and has been on rise constantly [1], despite the progress in systemic anti-tumor therapy for partial control or alleviation [2]. Notably, the advances in targeted therapies, driven by progressive genotype segmentation, have led to a de-chemotherapy era of molecular phenotypic personalization, represented by the third-generation epidermal growth factor receptor (EGFR) tyrosine kinase inhibitors (TKIs) such as Osimertinib, which has improved response rate (RR) to approximately 80% and prolonged median progress-free survival (PFS) to 10 $${\sim}$$ 14 months for the most common Ex19del with T790M [3, 4]. However, 79-88% of cases have suffered from adverse effects, whose toxicity led to multi-organs dysfunction and poor quality of life [5], disrupting the subsequent long-term use of this drug [6].

Fatigue is the most common adverse event reported by more than two-thirds of patients on Osimertinib [7, 8]. The significant correlation has been demonstrated between fatigue and worse overall survival (OS) in those with cancers, that probably attributed to the constant aggravation of fatigue as a result of clinical neglect and absence of invention, ultimately eroding the general state, and even leading to the termination of anti-tumor therapy [9, 10]. Currently, the principal therapies for fatigue include psychiatric medications, erythropoietin supplementation, and non-pharmacological methods such as exercise and psychotherapy [11]. Regrettably, these approaches are far from effective while lead to additional adverse events or induce malignancies [12]. Thus, it is imperative to optimize the efficacy of Osimertinib associated fatigue in non-squamous NSCLC patients with EGFR mutant.

Ganoderma lucidum spore powder (GLSP), one of the effective ingredients of traditional Chinese herb Ganoderma lucidum, is primarily known for its qi replenishing properties. GLSP has a variety of benefits including anti-inflammatory, antioxidant and immunomodulation [13], suggesting its anti-fatigue potential. Besides, GLSP can inhibit tumor progression, by regulating CD4^+^CD8^+^ T cell ratio and macrophage function, especially the expression of PD-1 in TIME.

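### PFS is a secondary efficacy endpoint but is followed only to day 84, about 20–28% of the cited median, so a PFS hazard ratio could neither support nor refute synergy

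*Protocol article*

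**What the plan says.** All references are to the Protocol article.

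- Secondary outcomes names ORR, DCR and "progression-free survival (PFS) according to RECIST 1.1 criteria" as the efficacy measures. It states that "Imaging examinations and efficacy assessments will be conducted on day 0, day 42, and day 84 of the treatment period" and that "PFS will be determined by follow-up at each treatment cycle during the follow-up period".
- Study design fixes the duration: "All participants will undergo two cycles of targeted and experimental drug therapy, followed by a one-month follow-up period". The Abstract agrees: "Following enrollment, visits are scheduled biweekly until week 12".
- Table 1 (Assessments and time-points) ends at day 84 with a window of ±7 days. It shows post-baseline imaging at days 42 and 84 only, and places day 84 in the follow-up period, 28 days after treatment.
- The Introduction says that osimertinib has "prolonged median progress-free survival (PFS) to 10" to 14 months for Ex19del with T790M.
- Study design also says: "The study is scheduled to be open from February 2023 until February 2026". Recruitment runs for 18 months from August 2023.
- The withdrawal criteria (Settings and participates) include rapid or radiographically confirmed progression. Statistical analysis says that data of participants who meet the withdrawal criteria are left out of the analysis. The same section mentions survival analysis, logistic and Cox models in general terms.

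**The concern.** Synergy with targeted therapy is in the title and in the stated purpose, and PFS is one of three measures that bear on it. If patients are watched for under three months when the cited median is 10 to 14 months, few will have an event, and the hazard ratio will have a confidence interval that includes both large benefit and large harm. Such a result could be read as showing no difference, or a chance imbalance could be read as benefit.

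Two further matters affect the same endpoint. The sentence on PFS speaks of treatment cycles during follow-up, although both cycles come before follow-up. The exclusion rule, read literally, would also remove the patients whose progression defines the endpoint.

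**Working it through.** **The plan's own figure.** The only design calculation is for the fatigue score: difference 15, SD 24.9, two-sided alpha 0.05, power 0.90. The noncentral t calculation gives 59 per arm (power 0.9006), and 59 / 0.85 = 69.4, rounded up to 70 per arm, or 140. This reproduces. No PFS event number, hazard ratio or power is stated.

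**Inputs.** N = 140, 70 per arm (Sample size calculation); last visit at day 84 (Table 1); median PFS m of 10 to 14 months (Introduction). Assumed, because the article does not give them: exponential PFS, no dropout, and hazard ratios (HR) of 0.70 and 0.50.

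**Length of the window.** 84 / 30.4375 = 2.76 months. 2.76 / 14 = 20% and 2.76 / 10 = 28% of the median.

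**Events under no effect.** P(event) = 1 − exp(−ln 2 × 2.76 / m).
- m = 10: 0.174, × 140 = 24.4
- m = 12: 0.147, × 140 = 20.6
- m = 14: 0.128, × 140 = 17.9

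**Events with an effect.** In the treated arm the rate is multiplied by HR, so the event count falls. At HR 0.70:
- m = 10: 70 × (0.174 + 0.125) = 21.0
- m = 14: 70 × (0.128 + 0.091) = 15.3

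**Log-rank power (Schoenfeld).** Power = Φ(√d / 2 × |ln HR| − 1.96), with d the events at that same HR.
- HR 0.70: √21.0 / 2 × 0.357 = 0.817, power 0.126; √15.3 / 2 × 0.357 = 0.698, power 0.104.
- HR 0.50 (18.6 and 13.6 events): power 0.32 and 0.25.
- For 80% power at HR 0.70, 247 events would be needed.
- Solving for the HR that gives 80% power, with the event count falling as HR falls: about 0.24 (m = 10, 15.3 events) and 0.18 (m = 14, 10.6 events).

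**Precision.** With d events split evenly, the 95% CI for the hazard ratio is the estimate times or divided by exp(1.96 × 2 / √d). For 24.4 events the factor is 2.21, and for 17.9 it is 2.53. An estimate of 1.0 would carry an interval of 0.45 to 2.21, or 0.40 to 2.53.

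**Sensitivity to dropout.** If only 118 patients contribute, 15–21 events are expected under no effect and 13–18 at HR 0.70, with power 9–11%.

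**Follow-up to study close.** Uniform entry over 18 months and closure in February 2026 give 12 to 30 months per patient. With rate λ, P(event) = 1 − [exp(−12λ) − exp(−30λ)] / (18λ).
- m = 10, HR 0.70: 70 × (0.751 + 0.627) = 96.5 events, power 0.42
- m = 14, HR 0.70: 70 × (0.635 + 0.509) = 80.1 events, power 0.36

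**The case against.** Several objections deserve weight.

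- **A secondary endpoint need not be powered.** This stands. The power figures only show how little the data can say; the defect is the short window, not a missing calculation.
- **The article does not assign a Cox model, a median or a hypothesis test to PFS.** Also true: Statistical analysis names the models generically. PFS is, however, the only time-to-event outcome named, so a hazard ratio is a likely product.
- **Follow-up may run longer than the visit table.** The study stays open for about a year after recruitment should end, so longer collection is feasible. The article specifies none, and it fixes follow-up at one month and visits at week 12.
- **The cited median belongs to another population.** It is given for Ex19del with T790M, whereas the intervention section describes initial treatment and the inclusion criteria name 19DEL and 21L858R. This is a real limit on the figures. A longer median would mean fewer events than shown here.

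A reader might also go further than the documents allow:

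- *The trial cannot address synergy at all.* Not so. ORR and DCR can be measured at days 42 and 84; only PFS is affected.
- *More than 80% of patients will be censored on one day.* Under the exponential model 83–87% have no event by day 84, but the plan allows 15% dropout and a ±7-day window, so censoring times will be spread.
- *Progression can be dated only to one of two scans.* The withdrawal criteria list rapid progression separately from radiographic confirmation, and deaths have their own dates.
- *The PFS data are worthless.* The curve read at day 84 gives a legitimate 12-week progression-free proportion.

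**Conclusion.** The point holds for PFS and for nothing wider. With the follow-up as stated, 18–24 events are expected under no effect and 15–21 at a hazard ratio of 0.70. Power at 0.70 is 10–13%, and only a hazard ratio of about 0.18–0.24 would be detected with 80% power. No median can be estimated in either arm, and no hazard ratio from these data should carry a conclusion about synergy.

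These figures rest on exponential PFS, a 10 to 14 month median taken from the Introduction, all 140 patients contributing, and the assumed hazard ratios. Dropout or a longer median would lower the event count. The primary fatigue endpoint is untouched by this point, so it should be corrected but does not threaten the trial's main question.

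**What to change.** 1. In Secondary outcomes, replace PFS by the proportion alive and progression-free at day 84, with the between-group difference and its 95% CI, labelled descriptive. Do not apply the Cox model from Statistical analysis to it, and draw no synergy conclusion from it.
2. For this endpoint, override the rule in Statistical analysis that leaves out participants who meet the withdrawal criteria: everyone who progresses or dies counts as an event. Without this, the proportion loses its own events and approaches 100% in both arms.
3. Reconcile the wording in Secondary outcomes that puts day 84 in the treatment period, and that refers to treatment cycles during follow-up, with Study design and Table 1, which place day 84 in follow-up after both cycles.

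These are text changes and cost almost nothing.

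Optional: keep PFS by collecting progression and death dates to February 2026, with progressors retained and the hazard ratio labelled exploratory. About 80–97 events and 36–42% power at a hazard ratio of 0.70 could be expected. This means record collection across thirteen hospitals beyond the stated one-month follow-up, so it has a real cost.

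### The QLQ-C30 total score sums over domains but divides by items, and no common direction is stated before the summing

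*Protocol article*

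**What the plan says.** The Secondary outcomes section of the protocol article lists the quality-of-life instruments together: "The QoL assessment will be conducted using the QLQ-C30, PFS-CV (Chinese version of the Piper Fatigue Scale), and EQ-5D (European Five Dimensional Health Scale". For the first of them it fixes a scoring rule: "The total score for QLQ-C30 is calculated by summing scores across domains and dividing by the number of items included". The sentence then adds a second step, "which is further linearly transformed using polarization", and does not define it. The text does not say which domains enter the total, which way each one runs, or whether any is reversed.

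The primary endpoint does not use this total: "The outcome endpoint will be determined based on the QLQ-C30 fatigue subscale score on day 56". That sentence also shows that fatigue is one of the QLQ-C30 subscales.

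On direction, the Introduction links fatigue to worse survival and a declining general state, and the Discussion treats it as harming quality of life. The Sample size calculation section, however, words the hoped-for benefit the other way: "The use of de-walled GLSP is assumed to result in at least a 15-point increase in fatigue score".

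**The concern.** Two things in the stated rule do not fit together.

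- **Numerator and denominator.** A sum of domain scores divided by a count of items is an average of nothing, unless every domain has exactly one item.
- **Direction.** The sum covers an instrument that includes fatigue, which the article itself regards as bad for quality of life. No step before the summing puts the domains on one direction. If functioning or global health domains run high = good while symptom domains run high = bad, an improvement in each pushes the total in opposite ways.

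At stake is whether this secondary score can be interpreted. Under the Statistical analysis section, a continuous score of this kind would be compared between arms by t-test or Wilcoxon test. A benefit on both fatigue and function could then show up as little difference, or with a sign that is hard to read. Because the sentence admits more than one reading, the scoring program could also be written in several ways, with different results.

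**Working it through.** **1. The plan's own figure.** The only related calculation in the article is the sample size. Its inputs, all from the Sample size calculation section, are "Two-Sample t-test Assuming Equal Variance (bilateral test", "alpha = 0.05, power = 0.90, and N1:N2 = 1:1 ratio", the SD from "a mean fatigue score of 32.2 ± 24.9 was observed", and a difference of 15 points.

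- Normal approximation: n per arm = 2 × (1.960 + 1.2816)² × (24.9/15)² = 2 × 10.507 × 2.7556 = 57.9, so 58.
- Two-sample t-test (noncentral t): 58.9, so 59 per arm, with power 0.9006 at 59.
- Dropout of 15%: 59/0.85 = 69.4, so 70 per arm and 140 in total.

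The stated 59 and 70 per arm reproduce. The total score is not an input, so nothing below changes them.

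**2. The denominator.** Let S_d be the score of domain d, D the number of domains and M the number of items. The literal rule is

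T = (S_1 + ... + S_D)/M = (D/M) × mean domain score.

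The article gives neither D nor M. Assuming D = 15 scales on 0-100 and M = 30 items, D/M = 0.5 and the largest possible T is 15 × 100/30 = 50. With D and M fixed, a later linear rescaling could undo this factor. If the items included are those a patient answered, M varies between patients and no fixed rescaling undoes it.

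**3. The direction.** Write the later step as U = a + bT. A change in U is b times the change in T, so two patients with equal T have equal U for any a and b. The step can stretch the total or flip its overall sign. It cannot separate components that have already cancelled.

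Smallest example, assuming one function domain is high = good and fatigue is high = bad: function rises by 10 and fatigue falls by 10, both improvements. The change in the sum is 10 - 10 = 0, whatever D, M, a and b are.

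**4. Size under assumed counts.** Suppose every scale improves by 10 points, with g scales high = good and h scales high = bad, g + h = 15, and M = 30. The literal change is 10(g - h)/30:

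| g / h | Literal total (sum/30) | Unreversed mean (sum/15) | Aligned mean |
|---|---|---|---|
| 15 / 0 | +5.0 | +10.0 | +10.0 |
| 8 / 7 | +0.33 | +0.67 | +10.0 |
| 6 / 9 | -1.0 | -2.0 | +10.0 |
| 0 / 15 | -5.0 | -10.0 | +10.0 |

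The working assumption is the 6 / 9 row; the others show the range. Cancellation is severe for any near-even split and absent only if all scales run the same way.

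**5. The alternative reading: raw items averaged first, then transformed.** Assume 28 items scored 1-4 with high = bad and 2 items scored 1-7 with high = good. Ten points on 0-100 is then 0.3 and 0.6 raw points. The change in the mean item score is (28 × (-0.3) + 2 × 0.6)/30 = -7.2/30 = -0.24. With all items aligned it would be (-8.4 - 1.2)/30 = -0.32. On this reading three quarters of the effect survives and its meaning is mostly coherent.

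**The case against.** The strongest reply is that the sentence is a clumsy account of ordinary scoring. Summing scores, dividing by the number of items and then transforming linearly is what one does within a single scale. On that reading nothing is added across domains and there is no cancellation. A mean of all raw items is another possible reading, and step 5 shows that it loses little. The transformation is undefined and might have been meant as the rescaling or aligning step. Scale counts, item counts and directions are not in the article, and scoring detail is commonly left to a fuller document.

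Much of this stands. The figures in steps 2, 4 and 5 are illustrations, and it cannot be said as fact that no domain is reversed, only that no reversal is stated before the summing. What does not stand is that the sentence can be left alone. It states a rule rather than omitting one. If per-scale scoring was meant, then calling the result a total, formed across domains, is wrong. If a mean of all items was meant, the sentence misdescribes what is summed. If it was meant literally, the denominator does not match, and an aligning step placed after the summing comes too late.

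A reader might also infer that the trial's quality-of-life outcome is worthless, or that its leading quality-of-life measure is lost. The article supports neither. It ranks none of the three instruments above the others, and PFS-CV and EQ-5D have their own scoring descriptions. Nor does the fault reach the primary endpoint, which is the fatigue subscale alone.

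**Conclusion.** The QLQ-C30 total score is wrongly defined as written. The mismatch between domains and items follows from the literal wording alone. The missing alignment before summing is also in the text, but its effect depends on the domains running in opposite directions. That is an assumption about the instrument, supported in part by the article's own treatment of fatigue as harmful to quality of life. The opposite wording in the sample size section is a further reason to state direction explicitly.

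Under the assumed 15 scales split 6 / 9 and 30 items, a uniform 10-point improvement would register as -1.0 instead of +10.0: a tenth of the size, with the sign reversed. Under the mean-of-items reading most of the effect would be kept. The point concerns one secondary score. It should be corrected before analysis, but it does not threaten the trial's main conclusion or its size.

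**What to change.** Replace the scoring sentence under Secondary outcomes. Suggested content: each QLQ-C30 scale is scored as the mean of its own items, linearly transformed to 0-100, with the direction of each scale stated, and the scales are analysed separately.

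If a single summary is also wanted, name the scales that enter it, align them to one direction before averaging (for example, 100 minus the score for scales where higher is worse), and divide by the number of scales. Either define the undefined transformation term or drop it.

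The cost is one sentence in the protocol, matching wording in the analysis plan, and a check of the scoring program. Data collection, sample size and the primary analysis do not change.
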